## Methods

### Study design

This feasibility randomised controlled trial is a 6-week study comparing the intervention (KOKU-LITE programme+dementia-specific falls prevention leaflet) with control (dementia-specific falls prevention leaflet) in community dwelling PLwD. After assessing participants for eligibility, they will be allocated randomly to either intervention group or control group. Assessments will be performed at baseline and 6 weeks follow-up (figure 1).

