### Outcome assessment

#### Primary outcomes

The feasibility and acceptability of the intervention will be evaluated in terms of recruitment, retention and adherence rates throughout the trial (table 1). Where possible, reasons underlying these rates will be documented.

**Table 1 T1:** Criteria for progressing to a larger trial

Feasibility	Go—proceed with RCT	Amend—proceed with changes	No go—do not proceed with RCT
Participant recruitment	N≥70 participants consent to the study	N=36–69 participants consent to the study	N≤35 participants consent to the study
Retention rate	≥75% remain in the study (ie, have not withdrawn)*	51%–74% remain in the study (ie, have not withdrawn)	≤50% remain in the study (ie, have not withdrawn)
Data collection	Target: ≥85% of participants from the study have all the study data collected	51%–84% of participants from the study have the study data collected	≤50% of participants from the study have the study data collected
Acceptability			
Engagement and acceptability	≥75% participants used KOKU-LITE intervention	51%–74% participants used KOKU-LITE intervention	≤50% participants used KOKU-LITE intervention

* Retention rate will be ≥75%, considering the patient population.

KOKU, Keep On Keep Up; RCT, randomised controlled trial.

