### Sample size

The total sample size for this study is 75 (60 PLwD for the feasibility study and 15 HSCPs for the interviews).

The intended sample size for the feasibility study will be 30 PLwD in each group, in which simple randomisation will be used with a 1:1 allocation. An attrition rate of 10%–20% is reasonable. A formal sample size calculation is not required as this study focuses on the practicalities of conducting the study. This number is pragmatic to assess the feasibility of the KOKU-LITE programme with the outcome measurements. It is anticipated that this sample size will provide sufficient information to inform a future definitive trial, assuming that the KOKU-LITE programme proves feasible and acceptable for PLwD.^35^

Up to 15 carers and HSCPs (including GPs, geriatricians, clinical psychologists, psychiatrists, community psychiatric nurses, community nurses, physiotherapists, occupational therapists and music therapists) will be recruited to evaluate the usability and acceptability of the app for this target population.

Feasibility of the KOKU-LITE intervention will be assessed based on the feasibility criteria outlined in table 1.^35^,^38^

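### Table 1's retention and data-collection criteria do not fit each other or the planned attrition, and retention defined by absence of withdrawal can be overstated

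*Protocol article*

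**What the plan says.** Recruitment, retention and adherence are the primary outcomes, and Table 1 (Primary outcomes) turns the feasibility measures into Go, Amend and No go bands. The Sample size section says that feasibility will be judged by that table.

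- **Retention, Go:** "≥75% remain in the study (ie, have not withdrawn". A footnote adds "Retention rate will be ≥75%, considering the patient population".
- **Data collection, Go:** "Target: ≥85% of participants from the study have all the study data collected".
- **Data collection, Amend:** "51%–84% of participants from the study have the study data collected". The requirement for all the data, present in the Go cell, is absent here and in the No go cell.
- **Planned attrition (Sample size):** "An attrition rate of 10%–20% is reasonable".
- **Size (Sample size):** "The intended sample size for the feasibility study will be 30 PLwD in each group, in which simple randomisation will be used with a 1:1", which makes 60 in total. The number is pragmatic: "A formal sample size calculation is not required as this study focuses on the practicalities of conducting the study".
- **Timing (Study design):** "Assessments will be performed at baseline and 6 weeks follow-up".

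The Data collection section keeps follow-up going for people who stop using the app. It does not mention people who cannot be contacted. The article does not say whether attrition means withdrawal or any missing 6-week assessment, nor how the rows of Table 1 combine into one decision.

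**The concern.** Table 1 decides whether a larger trial goes ahead, so each row should measure what its name says and the rows should be reachable together under the plan's own expectations. Two features work against this.

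The retention row counts the wrong event. In a community sample of people with dementia, loss can happen without a formal withdrawal. A rule that counts only withdrawals treats such people as retained, so a named primary outcome can look better than the follow-up that was achieved.

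The data row has no stated denominator. On the plain reading, all participants in the study, someone who leaves before the 6-week visit cannot have complete data. The data row then demands at least 85% retention for Go, although the row above accepts 75% with a footnote that appeals to the population. The same results could be classed as Go or Amend according to a definition that is not written down.

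**Working it through.** The thresholds and the 60 were set by judgement, so there is no power calculation to reproduce. The check converts the percentages to counts and asks which combinations are attainable.

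**Inputs.** N = 60, retention Go ≥75%, data Go ≥85%, attrition 10% to 20%, all from Table 1 and the Sample size section. Attrition is taken here to mean that no 6-week data exist.

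**Step 1: counts.** Retention Go: 0.75 × 60 = 45, so up to 15 may withdraw. Data Go: 0.85 × 60 = 51, so at most 9 may be incomplete if all 60 are the denominator. No count falls between bands at N = 60 (44/60 = 73.3%, 45/60 = 75%; 50/60 = 83.3%, 51/60 = 85%).

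**Step 2: ceiling on complete data, denominator all 60.** The largest possible complete share is 1 − attrition. The completeness needed among those remaining is 51 ÷ [60 × (1 − attrition)].

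- 10%: 54 remain; 51/54 = 94.4% must be complete.
- 15%: 51 remain; 51/51 = 100% must be complete.
- 20%: 48 remain; 51/48 = 106%, so Go is out of reach and the ceiling is 80%.

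With 45 to 50 retained (75% to 83.3%), retention is Go and data collection is at best Amend.

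**Step 3: chance of each Go.** Step 2 fixes the realised attrition. If attrition is instead a true underlying rate, the counts vary by chance: P(X ≥ k) for X ~ Binomial(60, p). For retention, k = 45 and p = 1 − attrition. For data, k = 51 and p = (1 − attrition) × completeness. The completeness figures are assumptions; the article gives none.

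| True attrition | P(retention Go) | P(data Go), 100% complete | 95% complete | 90% complete |
|---|---|---|---|---|
| 10% | 1.00 | 0.93 | 0.63 | 0.27 |
| 15% | 0.99 | 0.59 | 0.26 | 0.08 |
| 20% | 0.87 | 0.21 | 0.06 | 0.01 |

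**Step 4: the other denominator.** If 85% applies to those still in the study, it equals 0.85 × 0.90 = 76.5%, 0.85 × 0.85 = 72.3% and 0.85 × 0.80 = 68.0% of all 60 at 10%, 15% and 20% attrition. The conflict with the 75% retention cut disappears. The choice matters: with 48 retained and 41 of them complete, 41/48 = 85.4% is Go, while 41/60 = 68.3% is Amend.

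**Step 5: loss without withdrawal (illustrative counts).** With 6 withdrawn and 12 unreachable, retention as defined is (60 − 6)/60 = 90%, which is Go. Those with 6-week data number 60 − 18 = 42, or 70%, which would be Amend on the retention bands. With none withdrawn and 20 unreachable, the figures are 100% and 40/60 = 66.7%.

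**The case against.** The strongest reply is that the rows measure different things, so different cut-offs are not a logical contradiction. Retention Go with data Amend is a coherent mixed result, and both rows reach Go when at least 51 of 60 stay and at least 51 have complete data. This stands: the rows are misaligned, not contradictory.

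Four stronger readings are tempting and are not supported.

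- *A trial that runs as planned must miss the data row.* At 10% attrition a data Go is attainable, with probability 0.93 under perfect completeness. Only attrition above 15% excludes it, and only with all 60 as the denominator. Missing it then means Amend, which is proceeding with changes, not failure.
- *The 75% retention cut is redundant.* The article gives no rule for combining rows. The cut still decides its own row. It would cease to bind only if every row had to be Go and the data denominator were all participants.
- *Table 1 hides unreachable participants altogether.* They lack 6-week data and so lower the data row on either reading. In the illustration, that row is at most 42/60 = 70%, or 42/54 = 77.8% if the denominator is those not withdrawn. Only the retention row is flattered.
- *Pooled retention will conceal loss in one arm.* Weekly visits are described for the intervention only, but nothing says that retention will be reported only pooled. Reporting by arm is useful; requiring each arm to pass would be a design preference.

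It can also be said that the missing word in two cells is minor, because the bands are contiguous and suggest one measure. That is fair as to intent, but a participant lacking one instrument still has no clear classification outside the Go cell.

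**Conclusion.** The point holds in two parts. The first does not depend on any reading of the data row: defining retention by absence of withdrawal can overstate a primary outcome. By how much depends on how many are lost silently, which the documents do not let one estimate; the 90% against 70% is an illustration.

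The second is conditional. If the data row refers to all 60 participants, its Go level is out of reach once attrition passes 15%, the upper half of the planned range, while retention can still be Go. At a true rate of 20% the chances are 0.21 and 0.87 even with perfect completeness, and incomplete instruments widen the gap. If the row refers to those still in the study, there is no conflict, and the defect is that the denominator is unstated although it can change the classification. The figures rest on 60 participants, on withdrawal preceding the 6-week assessment, and on independent binomial loss at a common rate. This should be corrected, because the two rows feed the decision to proceed.

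**What to change.** 1. **Retention row.** Define retention as 6-week assessment completed divided by number randomised, in all three cells, and also report it by arm.
2. **Data-collection row.** State it as the percentage of retained participants with the study data complete, say what complete means, and use the same wording in all three cells. The 85% can then stay. With step 1 in place, each lost participant is counted once, in the retention row, and the data row measures completeness among those assessed.
3. **If all randomised is meant in the data row,** say so and align the 85% with the 75% retention cut and the 10% to 20% attrition. On that denominator complete data cannot exceed 75% at the retention cut, or 80% at 20% attrition.

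Recruitment has begun, so the change should be dated and made before the criteria are assessed. The cost is two rows of Table 1, with no new data and no change to the sample size. The downside is that the reported retention rate may be slightly lower than under the present definition.

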#### Secondary outcomes

The secondary outcomes will be assessed using standardised instruments and assessments (table 2).

**Table 2 T2:** Outcome measures

Outcome	Measure
Quality of life	Measured by The European Quality of Life 5 Dimensions (EQ-5D-5L) scale.^43^ EQ-5D-5L is a five-dimension version of the original EQ-5D scale. It has two sections: the EQ-5D descriptive system and the EQ visual analogue scale (EQ VAS). The descriptive system comprises five dimensions: mobility, self-care, usual activities, pain/discomfort and anxiety/depression. Each dimension has five levels: no problems, slight problems, moderate problems, severe problems and extreme problems. Current recommendations for scoring the EQ-5D-5L index will be followed. Index scores range from −0.59 to 1; 1 is the best possible health state. The EQ VAS records the patient’s self-rated health on a vertical VAS, where 0 indicates ‘worst health you can imagine’ and 100 indicates ‘the best health you can imagine’. Health-related quality of life will be measured at baseline and 6 weeks follow-up.
Activities of daily living	The Erlangen Test for Activities of Daily Living test (E-ADL-Test) is a valid and reliable instrument for assessing the ADL capabilities of people with dementia. It includes four domains: pouring a drink, cutting a piece of bread, opening a little cupboard, washing hands.^44^ The total score of the E-ADL ranges from 0 to 30, with a higher score representing better results. E-ADL-Test will be assessed at baseline and 6 weeks follow-up.
Functional mobility	The Short Physical Performance Battery (SPPB) is a validated and reliable instrument to assess functional mobility in people with cognitive impairment/dementia. The SPPB test includes three different domains: walking, sit-to-stand and balance.^45^ The scores range from 0 (worst performance) to 12 (best performance). Participants will be assessed at baseline and 6 weeks follow-up using SPPB.
Lower limb strength	Timed up and go (measurement of lower limb strength).
Confidence	The Short Falls Efficacy Scale-International (FES-I). The FES-I is a validated and reliable seven-item tool that measures confidence in performing a range of ADL without falling. This scale has recently been modified to maximise its suitability for a range of different languages and cultures.^46^ Scoring: minimum 7 (no concern about falling) to maximum 28 (severe concern about falling). FES-1 scale will be measured at baseline and 6 weeks follow-up.
Depression	The five-item Geriatric Depression Scale (GDS) screening tool for depression in older adults (validated to be as effective as the 15-item GDS for older adults in a wide range of settings.^47^ A score of 0–1 for the five-item GDS suggests that the subject is not depressed, while two or higher indicates possible depression. The five-item GDS screening tool will be measured at baseline and 6 weeks follow-up.
Falls risk	Falls risk will be measured with the use of the assessment of falls risk (FRAT) tool. This validated measure has five items that include: history of any fall in the previous year, four or more prescribed medications, diagnosis of stroke or Parkinson’s disease, reported problems with balance and inability to rise from a chair without using arms. These are all strong indicators for risk of falling.^48^ If a person scores 3 or more, they are at high risk of falling. FRAT tool will be measured at baseline and 6 weeks follow-up.
User experience	The User Experience Questionnaire (UEQ) is a standardised 26-item questionnaire that is used reliably to assess the quality and user experience of the interactive products.^49^ The standard interpretation of the scale means is that values between −0.8 and 0.8 represent a neural evaluation of the corresponding scale, values >0.8 represent a positive evaluation and values <−0.8 represent a negative evaluation. The range of the scales is between −3 (horribly bad) and +3 (extremely good). UEQ will only be measured at 6 weeks postfollow-up in the intervention group only (to those who use KOKU-LITE).

Quality of life will be measured using the European Quality of Life 5 Dimensions scale. In addition to the quality of life, participants’ activities of daily living (ADL) physical activity levels, functional ability, lower limb strength, fear of falling, falls risk, mood and user’s experience of the technology (KOKU-LITE app in this study) will be measured. Vision will be assessed using a self-reported question: “At the present time, would you say that your eyesight, using both eyes (with glasses or contact lenses if you wear them), is” (response options: excellent, good, fair, poor, very poor, registered blind).

#### Participant characteristics

Medical history (including fractures), medication comorbidities and demographic data (age, gender, ethnicity, socioeconomic status, etc) will also be recorded.

### Sample size

The total sample size for this study is 75 (60 PLwD for the feasibility study and 15 HSCPs for the interviews).

The intended sample size for the feasibility study will be 30 PLwD in each group, in which simple randomisation will be used with a 1:1 allocation. An attrition rate of 10%–20% is reasonable. A formal sample size calculation is not required as this study focuses on the practicalities of conducting the study. This number is pragmatic to assess the feasibility of the KOKU-LITE programme with the outcome measurements. It is anticipated that this sample size will provide sufficient information to inform a future definitive trial, assuming that the KOKU-LITE programme proves feasible and acceptable for PLwD.^35^

Up to 15 carers and HSCPs (including GPs, geriatricians, clinical psychologists, psychiatrists, community psychiatric nurses, community nurses, physiotherapists, occupational therapists and music therapists) will be recruited to evaluate the usability and acceptability of the app for this target population.

Feasibility of the KOKU-LITE intervention will be assessed based on the feasibility criteria outlined in table 1.^35^,^38^

### Blinding

Blinding of participants and researchers and outcome assessors will not be possible in this study due to the nature of the intervention and due to the lack of resources.

### Data collection

#### Quantitative research

Demographic data and standardised assessments/questionnaires will be completed at baseline and 6 weeks from both the intervention and control groups in participants’ homes by a member of the research team. Additional questionnaires about usability and motivation to use the app will also be completed at 6 weeks. Due to resource constraints, the same researchers will be responsible for delivering the intervention and collecting assessments/outcomes data. Follow-up outcomes data will be collected even if participants discontinue the use of the KOKU-LITE app.

#### Qualitative research

After 6 weeks of follow-up period, up to 15 participants who have expressed an interest from both the arms will be approached to take part in a semi-structured interview to:

talk about how the study was carried out and whether improvements could be made to the recruitment strategy, PIS, etc;discuss their views about the usability and acceptability of the KOKU programme. The interview will last approximately 60 min.

Carers and HSCPs (including GPs, geriatricians, clinical psychologists, admiral nurses, occupational therapists, etc) will be invited to attend up to three focus groups, lasting up to 60 min. The aim of the focus group is to gather their views about how usable and acceptable the app might be for PLwD, and any changes they would suggest making it suitable for this population.

Semi-structured interviews and focus groups will be conducted either face-to-face or through online platforms (such as MS Teams or Zoom), according to each interviewee’s preference (and in compliance with any restrictions in place due to COVID-19). Interviews or focus groups will last up to 60 min. Interviews or focus groups will be recorded (audio) with participant’s permission. If an online platform is used, participants will be asked to turn off the video after the researcher and participant introductions. The topic guides used to conduct the interviews will be informed by the literature and our previous work. The topic guide (for PLwD and carers) will be piloted with the Project Advisory Group.

### Analysis

#### Quantitative research

Analysis will be descriptive. Baseline characteristics and postintervention data will be summarised, as appropriate, using means (with SD) or median (IQR). For dichotomous or categorical data, frequency will be reported by number or percentage of responses within each category. Calculations will be conducted using SPSS V.29.

As this is a feasibility study, formal hypothesis testing will not be conducted for secondary outcomes, which include changes in health-related quality of life, ADL, physical activity, functional ability and other fall-related measures. Instead, intervention effects will be summarised using point estimates and their corresponding SDs. These estimates will be calculated as the unadjusted mean differences between baseline and each postintervention timepoint. The resulting summary statistics will inform sample size calculations for a future definitive trial, if progression criteria are met. Basic statistical comparisons of pre-intervention and post-intervention outcomes will be performed to describe trends, applying an intention-to-treat approach to ensure that participants are analysed according to their original group allocation.

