## Aim

To test the feasibility of the KOKU-LITE digital programme with PLwD aimed at preventing falls and improving well-being compared with control (a dementia-specific falls prevention leaflet).

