## Objectives

Explore study recruitment approaches for PLwD, their carers and health and social care professionals (HSCPs) for the feasibility study.Explore the specific training and support needs of PLwD, their carers and HSCPs to enable effective use of KOKU-LITE during the feasibility phase. Particular attention will be paid to the distinct and additional requirements associated with engaging in digital exercises and interactive games on the tablet/iPad, ensuring accessibility and sustained engagement.Explore the usability and acceptability of the KOKU-LITE programme.Describe and determine the suitability of the outcome measures including providing data to permit estimation of effect size to be used in sample size calculations for a definitive trial.

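### The effect on secondary outcomes is defined as change from baseline with an SD, not as the difference between randomised arms with a confidence interval

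*Protocol article*

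**What the plan says.** The quantitative Analysis section states that "intervention effects will be summarised using point estimates and their corresponding SDs", and defines these quantities in the next sentence: "These estimates will be calculated as the unadjusted mean differences between baseline and each postintervention timepoint". On their use it says: "The resulting summary statistics will inform sample size calculations for a future definitive trial, if progression criteria are met". It then adds: "Basic statistical comparisons of pre-intervention and post-intervention outcomes will be performed to describe trends, applying an intention-to-treat approach", with participants kept in the group to which they were allocated. It also says that "formal hypothesis testing will not be conducted for secondary outcomes".

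The Aim and Study design sections describe a randomised comparison of KOKU-LITE plus leaflet against leaflet alone. One objective is "providing data to permit estimation of effect size to be used in sample size calculations for a definitive trial". Assessments take place at baseline and 6 weeks in both arms (Study design; Data collection), so 6 weeks is the only post-intervention time point. The article defines no between-arm difference and no confidence interval for any secondary outcome.

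**The concern.** The definition contrasts two times, not two arms. Change within an arm combines whatever the intervention does with everything else that happens over 6 weeks: familiarity with performance tests such as the SPPB, timed up and go and E-ADL, regression to the mean, and progression of dementia. The randomised control arm exists to remove what both arms share, and the stated definition does not use it for that purpose.

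The summary attached to the effect is also the wrong kind. An SD describes spread between participants and does not shrink as the sample grows. It cannot tell a reader how uncertain the estimated effect is.

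At stake is the use that the protocol itself names. A definitive randomised trial is sized on the difference between arms. If change from baseline is carried forward as the effect, the planned sample may be far too small or unnecessarily large.

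**Working it through.** **No stated figure to reproduce.** The Sample size section gives a pragmatic 30 per arm, expects 10%–20% attrition, and states no effect size, SD, alpha or power. The check is therefore a reading of the text, followed by an illustration on assumed values.

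**1. Reading the sections together.**
- Aim and Study design: the comparison is between two randomised arms.
- Objectives: data are wanted for an effect size to plan a definitive trial.
- Analysis: the effect is the mean difference between baseline and follow-up, unadjusted, with an SD.
- Analysis, last sentence: the only other comparison named is again before against after, with participants kept in their allocated group.

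The first two call for a between-arm contrast, and the Analysis section defines something else. The article states this definition outright, so it is not a detail left to a separate analysis plan.

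**2. What the two quantities measure.** Let c be the mean change in the control arm and θ the true between-arm effect. The mean change in the intervention arm is then θ + c. It equals θ only if c = 0, and c can be positive (practice, regression to the mean) or negative (disease progression).

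**3. Consequence for sample size.** Assumptions: intervention-arm change of 0.5 in units of the SD of change, two-sided alpha 5%, power 80%, 1:1 allocation, and a planner who takes that change as the effect. With the normal approximation, n per arm = 2(1.96 + 0.842)² / d² ≈ 15.70 / d².

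Sizing on d = 0.5 gives 15.70 / 0.25 = 62.8, so 63 per arm (64 with the t distribution). The true contrast is 0.5 − c:

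| Control change c | True contrast | n per arm needed | Power with 63 per arm |
|---|---|---|---|
| +0.3 | 0.2 | 393 | 20% |
| +0.2 | 0.3 | 175 | 39% |
| +0.1 | 0.4 | 99 | 61% |
| 0 | 0.5 | 63 | 80% |
| −0.1 | 0.6 | 44 | above 80% |
| −0.2 | 0.7 | 33 | above 80% |

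Power is Φ(d√(63/2) − 1.96). For d = 0.3 this is Φ(5.61 × 0.3 − 1.96) = Φ(−0.28) = 39%.

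**4. What a confidence interval would show.** The unadjusted 95% half-width for an arm difference, in SD units, is t(0.975, 2n − 2) × √(2/n).

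| n per arm | Basis | √(2/n), the SE as a fraction of the SD | 95% half-width |
|---|---|---|---|
| 30 | no attrition | 0.26 | 0.52 SD |
| 27 | 10% attrition | 0.27 | 0.55 SD |
| 24 | 20% attrition | 0.29 | 0.58 SD |

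The planned point estimate with an SD does not display this uncertainty.

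**The case against.** The strongest defence is that this is a descriptive feasibility study. The article says that it is not powered for effectiveness, and neither the primary outcomes nor the Table 1 progression criteria use these estimates. That stands and limits the severity. It does not justify the definition, because a between-arm difference with an interval is also descriptive and needs no test.

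Several stronger readings are tempting, but the documents do not support them:

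- *That the control arm goes unused.* Both arms are assessed at both times, and participants are analysed by original allocation, so changes by arm will probably be shown. Mean change, SD and n by arm would let a reader derive the difference and its interval. The fault is narrower: the protocol does not name that difference as the effect.
- *That reporting an SD is itself an error.* An SD is a legitimate input to sample size planning and should stay. The fault is that it stands where a measure of precision is needed.
- *That the section promises no testing and then plans tests.* It says "Basic statistical comparisons of pre-intervention and post-intervention outcomes will be performed to describe trends". The wording is loose, but no test or p-value is named, so a contradiction is not established.
- *That the effect will be overstated.* Controls may decline as well as improve, so the direction is unknown. Nor does the protocol say that a planner would put the raw intervention-arm change into a two-sample formula.

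Two further limits are fair. Under randomisation an unadjusted between-arm difference in change is also valid, so baseline adjustment is a preference for precision. And an arm contrast removes only what the arms share: it would not remove the influence of weekly researcher visits to the intervention arm or of unblinded assessment.

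**Conclusion.** The point holds as a should-fix. The Analysis section fixes the intervention effect on secondary outcomes as a change over time, although the aim, design and effect-size objective call for a contrast between arms, and it gives no interval for that effect. With an assumed intervention-arm change of 0.5 SD and control changes from +0.3 to −0.2 SD, the required size ranges from 393 down to 33 per arm, against 63 if the change is taken as the effect. These control changes are assumptions, because the article gives none. The size of the error in practice is therefore unknown, and so is its direction.

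**What to change.** Reword the paragraph as follows:

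- For each continuous secondary outcome measured in both arms at baseline and 6 weeks, define the effect as the between-arm difference at 6 weeks, as randomised and adjusted for the baseline value, with a 95% CI and no p-value. This excludes the UEQ, which is collected only at 6 weeks and only in the intervention arm.
- Keep the arm-specific SDs and add the baseline-to-6-week correlation, since both are needed for planning.
- Limit before-and-after comparisons to descriptive summaries by arm.
- Replace the reference to each post-intervention time point with 6 weeks.

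The cost is one rewritten paragraph and a standard analysis of data already being collected. There is a small downside: with 24–30 analysed per arm the unadjusted half-width is about 0.52–0.58 SD, so the estimate will be imprecise and could be over-read. The text should say that it is to be read through its interval and not used alone to size the definitive trial.
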